### 7.3 Criteria for treatment discontinuation in individual subjects

If the investigational treatment cannot be continued in individual subjects for reasons listed below, the physician in charge is to discontinue the treatment in these subjects, record the date of discontinuance along with the reasons for discontinuance, and report to the Data Center.

- Occurrence of a serious macrovascular or microvascular disease
- Occurrence of one other serious complicating disease
- Diagnosis or strong suspicion of type 1 diabetes (including slowly progressive IDDM; SPIDDM)
- Difficulties continuing treatment due to adverse reactions
- Patient request for discontinuance
- Patient death
- Other cases in which the physician in charge judged continued treatment difficult

Even when the investigational treatment was discontinued in a particular subject, with the subject's consent (for subjects who are incompetent, consent from the family member or legally authorized representative), the subject can be followed up on the presence or absence of events set forth in section 10 as the primary and secondary endpoints of the study. In which case, in accordance with the observation/evaluation schedule laid down in section 9, serum creatinine, urinary albumin and urinary creatinine are to be measured, and funduscopy and ECG exams to be performed in the subject.

If any subject ceases to present at the host hospital, the physician in charge is to inquire the subject by phone or mail as to his/her reasons for not presenting and to confirm his/her willingness to continue to participate in the study (if the subject is able to resume his/her regular visits, encourage him/her to do so). If, however, the subject is judged to be having difficulty continuing the investigational treatment, the physician in charge is to determine whether or not the subject had any of the events described in section 10. If the subject was found to be dead, the physician in charge is to look into the date, cause and location (home address) of death of the subject. As soon as the physician in charge found it difficult to make any further survey on the subject, he/she is to make entries in the medical record about when, how and why the subject discontinued the investigational treatment, as well as if the subject had any of the events set forth in section 10 at the time of treatment discontinuation, and report to the Data Center.

If the subject was found to have moved out or changed hospital, the physician in charge is to identify the location of the subject as well as the hospital through appropriate means, and inquire the subject as to his/her willingness to continue with the investigational treatment, and determine whether or not the subject had any event, in much the same way as the physician in charge is to deal with a subject ceasing to present at the hospital. As soon as the physician in charge found it difficult to make any further survey on the subject, he/she is to make entries in the medical record about when, how and why the subject discontinued the investigational treatment, as well as whether or not the subject had any event at the time of treatment discontinuation, and report to the Data Center.

If the physician in charge had any difficulty obtaining information about the subject from the new hospital, the Data Center is to consider intervening to get necessary information as required. In which case, however, the Data Center is to ask that the physician in charge at the new hospital obtain consent from the subject (for subjects who are incompetent, consent from the family member or legally authorized representative) himself/herself regarding release of the information being sought. Alternatively, the Data Center is to contact the subject (for subjects who are incompetent, the family member or legally authorized representative) directly to obtain such information.

If the Data Center had any difficulty following up on the subject, the Data Center is to consider sending a Clinical Research Leader-designated agent to find out whether or not the subject is dead or alive where he/she lives by consulting the Basic Residence Register. Additionally, if permission is obtained to do so from the Ministry of Internal Affairs and Communications, the Data Center is to consider sending a Clinical Research Leader-designated agent to look into the cause of death of the subject by consulting the Vital Statistics. The processes through which to implement these inquiries, along with that that concerns protection of the subject's privacy, are described elsewhere.

## **8. Investigational treatment**

The investigational treatment in this study is defined as "intensive multi-factorial therapy" with "conventional therapy" serving as the reference/control treatment, where each treatment is intended to achieve lifestyle modification (weight reduction, diet restriction, exercise therapy and smoking cessation) as well as glycemic, blood pressure and lipid control as described below. In using pharmacologic agents for glycemic, blood pressure and lipid control, it is essential that relevant package inserts be consulted to ensure that they are not used in patients in whom their use is contraindicated.

### **8.1 Guidance on lifestyle modification**

#### **8.1.1 Weight reduction**

All subjects in both treatment arms are to be provided with patient diaries to record their own body weight.

In the intensive therapy arm, where the management goal for BMI is set for 22 or less, all subjects are obliged to measure their body weight at a predetermined time once daily, record and report on the measurement, and the physician in charge is to keep informed of these measurements.

In the conventional therapy arm, where the management goal for BMI is set for 24 or less, all subjects are also obliged, as are those in the investigational treatment arm, to measure their body weight, record and report on the measurement, and the physician in charge is to keep informed of these measurements.

Once the management goal for BMI (body weight) has been achieved in any patients in either arm, BMI is to be maintained at that level. In those complicating diabetic nephropathy, the management goal is to be achieved by drawing on the diet criteria for diabetic nephropathy.

Between-meal and bedtime snacks are to be prohibited as a rule, except where they are required to avoid hypoglycemia associated with the use of oral anti-diabetic drugs or insulin therapy.

#### **8.1.2 Diet restriction**

Total energy intake is to be rigorously controlled in the subjects in the intensive therapy arm. Specifically, in those with BMI 25 or greater at study entry, the management goal for diet restriction is set for "25 kcal/1 kg of ideal body weight (IBW)", and in those with BMI less than 25, the goal for diet restriction is set for "27 kcal/1 kg of ideal body weight (IBW)".

In this regard, the subjects in the intensive therapy arm are to be instructed in person that through diet restriction, lipid is to account for less than 25% of total energy intake, with cholesterol intake accounting for 300 mg/day or less and salt intake accounting for 6 g/day or less. Additionally, they are to be instructed that between-meal and bedtime snacks are to be prohibited, and alcohol abstinence (equivalent to 180 mL of sake or less) is to be adhered to, and they are obliged to report on alcohol intake at regular hospital visits.

Additionally, they are to be given 30-minute or longer guidance on nutrition by the designated national registered dietitians at the start of the study, 1, 3, 6 and 12 months after the start of the study and every 6 months in the second year afterwards (a separate manual on nutritional guidance is to be developed to ensure consistency in their approach).

The subjects in the conventional therapy arm are to be instructed about the total energy intake to be adhered to in accordance with the Japan Diabetes Society Clinical Practice Guidelines (hereafter Guidelines). Salt restriction is also to be encouraged as required.

Subjects in both arms are to be instructed on allowable diets using the "Food Exchange Lists - Dietary Guidance for Persons with Diabetes (7th edition)" edited by the Japan Diabetes Society. Again, those with diabetic nephropathy in both arms are to be encouraged to restrict protein intake in accordance with the "A Guide to the Management of Diabetes" edited by the Japan Diabetes Society.

#### **8.1.3 Exercise therapy**

All subjects in both treatment arms are to be loaned an accelerometer at study entry.

The subjects in the intensive therapy arm are to be instructed to walk 15 to 30 minutes twice or more frequently per day. As a rule, the subjects are obliged to walk every day and to report on the calorie consumed as well as the number of steps taken every day. The physicians or nurses in charge are to keep informed of their activity status so that it can be borne in mind when giving exercise instructions.

The subjects in the conventional therapy arm are to be instructed in accordance with the Guidelines.

#### **8.1.4 Smoking cessation**

All subjects in the intensive therapy arm are to be instructed to persevere in their smoking cessation practice and to report on the number of cigarettes smoked at their regular hospital visits. Those who find smoking cessation difficult are to be encouraged to use smoking-cessation aids.

#### **8.1.5 Implementation of the core program**

To ensure that the goals for lifestyle modification (weight reduction, dietary restriction, exercise and smoking cessation) are met in the intensive therapy arm, a core program intended to improve lifestyle habits is to be implemented to ensure lifestyle factors are improved in the subjects. A post-core program will also be implemented after completion of the core program to ensure lifestyle factors are further improved in the subjects. Details of the core program are given elsewhere.

## 8.2 Glycemic control

### 8.2.1 Intensive therapy

In the intensive therapy arm, the goal for glycemic control is defined as HbA1c < 6.2% and the subjects are to make regular hospital visits for glycemic control and monitoring (see Note 1). If any of the subjects receiving treatment on an outpatient basis does not achieve the management goals, they will be immediately hospitalized to ensure better glycemic control in these subjects.

Furthermore, all subjects in the intensive therapy arm are to be loaned a blood glucose meter for self-monitoring of blood glucose (SMBG), and the physicians in charge are to keep informed of the measured results in these subjects.

All subjects are to be treated first with predetermined diet and exercise therapy, and if they fail to achieve HbA1c < 6.2% in the first 3 months, they will be given anti-diabetic drugs in the following steps (those already on anti-diabetic drugs at study entry are to continue with the medication and be treated with lifestyle modification to achieve their respective management goals). Anti-diabetic drugs to be used include thiazolidinedione derivatives, biguanides, sulfonylureas, rapid-onset insulin secretagogues (glinides),  $\alpha$ -glucosidase inhibitors, DPP-4 inhibitors, SGLT2 inhibitors, GLP-1 receptor antagonists and insulin. Of these, sulfonylureas and glinides are both designated as "insulin secretagogues" and DPP-4 inhibitors and GLP-1 receptor agonists are designated as "incretin-related drugs."

The treatment specified in each of the steps is to be continued if the treatment leads to HbA1c < 6.2% or a  $\geq 1\%$  decrease in HbA1c within 6 months for the subjects. If, however, the goal of HbA1c < 6.2% cannot be achieved with treatment and if treatment is associated with a less than 1% decrease in HbA1c, the treatment is to be intensified to the next step (refer to Notes 1 and 2 if only one of the goals is achieved). In any of the steps described, the dosage may be increased, decreased, discontinued or changed (see Note 2), and an  $\alpha$ -glucosidase inhibitor, DPP-4 inhibitor, or SGLT2 inhibitor may be added at the discretion of the physician in charge. For instructions on the addition of a biguanide or GLP-1 receptor agonist, see Note 3 and, for directions for use of incretin-related drugs, see Note 4.

The thiazolidinedione derivative pioglitazone is to be given up to 30 mg/day as a standard maximal dose but the dose can be further increased to 45 mg/day if the physician in charge finds it necessary. However, utmost care is to be taken in increasing the dose from 30 mg to 45 mg/day.

Again, if the physician in charge finds it necessary, temporary or continued insulin therapy can be given (this constitutes step 3). In this case, however, a thiazolidinedione derivative is to be used in combination as long as that is possible. Whether or not to use a thiazolidinedione in combination is to be decided at the discretion of the physician in charge.

In any of the steps described below, diet and exercise therapy is to be continued.

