**Glycemic control**

If each of the steps described below achieves an HbA1c value of less than 6.2% or a 1% reduction in HbA1c values in the subjects within 6 months, that treatment is to be continued; and if not, the treatment is intensified to the next step.

Pioglitazone which is associated with a certain level of evidence that supports their use in the reduction of macrovascular complications are to be chosen whenever possible.

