### **Dose reduction and discontinuation of anti-diabetic drugs**

The physician in charge is to carefully watch for episodes of hypoglycemia in all subjects receiving anti-diabetic drugs, and to adequately educate the subjects on how to deal with these episodes when they appear. In the subjects with frequent hypoglycemia, every effort is to be made to immediately optimize drug therapy by having them consult the physician in charge as often as possible or by hospitalizing them. In optimizing drug therapy, the decision as to which drug needs to be discontinued or reduced is to be left up to the physician in charge. However, even when the physician in charge makes such a decision, he/she is to avoid discontinuing the thiazolidinedione derivative already being used whenever possible. When fluid retention occurs likely due to the use of a thiazolidinedione derivative, the physician in charge is to deal with it by giving a diuretic or by reducing or discontinuing the thiazolidinedione derivative at his discretion.

Note 1: If the goal of HbA1c < 6.2% has been achieved with drug therapy, that particular treatment is to be continued. However, the decision is left up to the physician in charge on whether or not to increase, reduce or discontinue a particular drug, replace a sulfonylurea with a glinide or vice versa, switch treatment among a thiazolidinedione derivative, biguanide, or GLP-1 receptor agonist, replace a drug with another within the same drug class, or add an  $\alpha$ -glucosidase inhibitor, DPP-4 inhibitor, SGLT2 inhibitor, biguanide, or GLP-1 receptor agonist. When HbA1c becomes 6.2% or greater in a particular subject, every effort is to be made to ensure that HbA1c is maintained below 6.2% by implementing more intensive therapy (more rigorous lifestyle modification, dose increases or replacements). In the event that HbA1c becomes 6.2% or greater on 3 consecutive measurements despite this intensive therapy in a particular subject, it is to be deemed difficult to achieve the predetermined management goals in this patient, the treatment is intensified to the next step depending on the management goals achieved in this patient as follows:

Diet/exercise therapy (+ $\alpha$ -glucosidase inhibitor, DPP-4 inhibitor and/or SGLT2 inhibitor) (considered as step 0) → step 1

1 anti-diabetic drug (+ $\alpha$ -glucosidase inhibitor, DPP-4 inhibitor and/or SGLT2 inhibitor) (considered as step 1) → step 2

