**11.4 Serious adverse reactions****11.4.1 Technical terminology**

Any adverse reaction is defined as serious adverse reactions, if it:

|                                                                                                                                                                                                                                |
|--------------------------------------------------------------------------------------------------------------------------------------------------------------------------------------------------------------------------------|
| Is fatal                                                                                                                                                                                                                       |
| Is life-threatening                                                                                                                                                                                                            |
| Leads to the subject becoming hospitalized or calling for prolonged hospitalization or treatment                                                                                                                               |
| Leads to permanent or serious damage or dysfunction in the subject                                                                                                                                                             |
| Causes congenital anomaly                                                                                                                                                                                                      |
| Is serious hypoglycemia accompanied by impaired consciousness                                                                                                                                                                  |
| Is some other serious medical phenomenon                                                                                                                                                                                       |
| Or is serious enough to place the subject in a critical situation calling for treatment to avoid the outcomes described above, while it is not immediately fatal, life-threatening or leads to the subject being hospitalized. |

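### Section 8.2.1 orders immediate hospitalisation of intensive-arm outpatients who miss the goals, which contradicts the protocol's own timed, stepwise rules for the same situation

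*Protocol*

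**What the plan says.** The hospitalisation sentence is in the opening paragraph of Protocol 8.2.1. Its condition is "If any of the subjects receiving treatment on an outpatient basis does not achieve the management goals" and its consequence is "they will be immediately hospitalized to ensure better glycemic control in these subjects". The goal in that section is HbA1c below 6.2%.

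The same section and its notes also give these rules for a subject who is off goal:

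- Diet and exercise come first: "if they fail to achieve HbA1c < 6.2% in the first 3 months, they will be given anti-diabetic drugs in the following steps".
- Within a step, treatment continues if HbA1c falls below 6.2% or drops by at least 1% within 6 months. If neither happens, "if treatment is associated with a less than 1% decrease in HbA1c, the treatment is to be intensified to the next step".
- Note 1 after Step 3 sets outpatient visits at least monthly until March 2010. After that, visits stay monthly for patients with unstable control, while stable patients who have nearly reached the goals may attend up to 3 months apart (insulin users excepted).
- Under the heading on dose reduction and discontinuation, Note 1 first tightens lifestyle and drug treatment after a relapse. It moves the patient to the next step only when "HbA1c becomes 6.2% or greater on 3 consecutive measurements despite this intensive therapy". Note 2 keeps the same treatment for a further 6 months after a fall of more than 1%.

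The glycaemic part of the regimen outline at the front of the protocol gives only continuation or step-up: "that treatment is to be continued; and if not, the treatment is intensified to the next step". It has no admission for a missed goal.

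Section 8.2.2, for the conventional arm, has no hospitalisation rule. Section 11.4.1 lists this among the criteria that make an adverse reaction serious: "Leads to the subject becoming hospitalized or calling for prolonged hospitalization or treatment".

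**The concern.** This is a treatment instruction that sites must act on, so a statistical analysis plan would not settle it. One site may admit every outpatient found off goal, another may follow the steps, and both can cite section 8.2.1. The intensive arm would then mix two strategies in unknown proportions. An effect estimate, for benefit or harm, could not be tied to one defined intervention.

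A second, smaller issue concerns safety. The admission rule applies in one arm only, the trial is open-label (section 6.1), and hospitalisation bears on seriousness. Serious reactions also feed oversight during the trial: section 11.4.3 asks whether their frequency is within the anticipated range, and section 19.6 has their incidence reported to Trial Progress Management. If some of them come from admissions that the protocol itself ordered, the counts need to be readable with and without those admissions.

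**Working it through.** The plan gives no figure to reproduce here, so the check sets the rules side by side for each situation in which an intensive-arm outpatient is off goal.

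1. **Off goal during or at the end of the first 3 months.** The step rules continue diet and exercise to 3 months and then start drugs. The hospitalisation sentence admits the patient, with no time stated.

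2. **Off goal after 6 months in a step, HbA1c down by at least 1%.** The step rules keep the same treatment; the hospitalisation sentence admits. Taking the 1% as percentage points, this arises for any starting value of 6.2 + 1.0 = 7.2% or more. For example, a subject who starts at 8.9% (the allocation cut-point in section 8.6) and falls by 1.0 reaches 8.9 − 1.0 = 7.9%. That is 7.9 − 6.2 = 1.7 points above goal. One rule continues treatment unchanged and the other admits.

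3. **Off goal after 6 months in a step, HbA1c down by less than 1%.** The step rules move to the next step; the hospitalisation sentence admits. Both could be done together, but no passage says so.

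4. **Stable and close to goal, not on insulin, after March 2010.** The visit note allows up to 3 months between visits; the hospitalisation sentence admits at once.

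5. **Relapse after the goal was reached.** The notes intensify treatment, wait for three consecutive off-goal values and then step up. If the hospitalisation sentence applies to a relapse, it does not wait.

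Situations 2 and 4 conflict directly. Situations 1 and 5 conflict on timing unless the sentence is given a trigger that it does not contain. Situation 3 is compatible only by adding something unwritten. The sentence is also not worded as optional. Where the protocol wants an alternative it states one: for frequent hypoglycaemia it offers closer consultation or hospitalisation.

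For the safety point, each link was checked in turn:

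- **One-sided rule:** yes (8.2.1 against 8.2.2), in an open-label trial (6.1).
- **Is an admission in itself a serious adverse reaction?** No. Section 11.4.1 grades an adverse reaction that already exists.
- **Can off-goal HbA1c be recorded as an adverse reaction?** Possibly. Section 11.1 includes untoward laboratory findings after the start of the study. Section 11.2, Procedure 3, looks for new or worsened findings and leaves it to the physician which laboratory changes are clinically meaningful.
- **Is there an exemption for off-goal HbA1c or protocol-ordered admissions?** None is stated in sections 11.1 to 11.4.
- **What is tested?** Section 12.3.3 compares the percentages with adverse reactions by Fisher's method and does not mention serious ones separately.

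For scale, each 1% of the 1,271 intensive-arm subjects admitted under the sentence would be 0.01 × 1,271 = 12.7, about 13 subjects. The protocol gives neither an expected admission rate nor a background rate of serious reactions, so no size can be put on the effect.

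**The case against.** The strongest defence is that hospitalisation is a setting while the steps define the regimen, so a subject can be admitted and stepped up together. This holds for situation 3. It does not help where the step rules say to leave treatment unchanged, or to see a nearly controlled patient up to three months later.

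A reader might infer that every intensive-arm subject must be admitted at entry, because entry requires HbA1c of 6.9% or more and the goal is below 6.2%. The text does not support this well. The sentence concerns subjects already receiving outpatient treatment who fail to reach the goals, and the same section says that all subjects start with diet and exercise.

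A reader might also infer that the safety comparison is tilted against intensive therapy. The documents do not establish that. Seriousness attaches to an adverse reaction and not to an admission. A subject who stays above goal without worsening has no evident new finding. The comparison in section 12.3.3 is of adverse reactions overall, and upgrading a recorded reaction to serious leaves that percentage unchanged. Case-report procedures are left to a standard operating procedure that is not shown (section 15.1), and it may settle the coding.

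Finally, in a strategy trial, admissions that the strategy requires are part of its burden, and removing them from serious counts could understate it. That objection stands, so the remedy is to show them separately and not to exclude them.

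**Conclusion.** The contradiction in the treatment rule holds. As written, the hospitalisation sentence in section 8.2.1 cannot be followed together with the rules for continued off-goal treatment and for widely spaced visits. Its missing trigger also puts it at odds with the 3-month first phase and, if it covers relapse, with the three-measurement rule. This rests on the text alone and needs no assumed rates. How far sites actually diverged is unknown from the protocol.

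The safety point holds only conditionally. It requires that off-goal or worsening HbA1c, or another condition leading to such an admission, is recorded as an adverse reaction, and that serious reactions are then read by arm. Any distortion would then raise the intensive-arm count. The document does not show that this happens and does not describe a formal between-arm test of serious reactions.

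**What to change.** Reconcile the hospitalisation sentence in section 8.2.1 with the glycaemic step rules in the front outline, with Steps 0 to 3 and their notes, and with the notes on dose reduction and discontinuation. One rule should then apply when the goal is missed. Which rule that is belongs to the clinical team.

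In section 11, record the reason for admission in the same way in both arms. Tabulate admissions for glycaemic optimisation separately, so that serious adverse reaction counts can be read with and without them.

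The cost is a wording change in the protocol, one reason-for-admission field on the serious-event form, and one extra safety table. Sample size, the primary endpoint and the primary analysis are unaffected.

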### **8.2.2 Conventional therapy**

The goal for glycemic control in the conventional therapy arm is defined as HbA1c < 6.9%, and the physician in charge is to administer appropriate therapy in accordance with the Guidelines.

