### 8.3 Blood pressure control

All the subjects in both treatment arms are to be loaned a blood pressure manometer at study entry.

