## 11. Safety evaluation

### 11.1 Technical terminology

In the present study, “adverse reactions” and “side effects” are defined as followed.

- Adverse reactions

Adverse reactions are defined as any untoward (or unintended) symptoms and signs (including abnormal laboratory findings) that may or may not be causally related to the investigational treatment. In other words, all untoward symptoms or signs that occurred in the study subjects, including those whose causal relationship to the investigational treatment can be ruled out, are to be recorded as “adverse reactions”.

In this trial, all untoward laboratory findings that occurred after the start of the study are to be handled as adverse reactions, in addition to all symptoms and signs that newly occurred or worsened after the start of the study.

- Side effects

Of the untoward (or unintended) symptoms and signs (including abnormal laboratory findings), those whose causal relationship to the investigational treatment cannot be ruled out are defined as side effects. In other words, of the “adverse reactions” defined above, those whose causal relationship to the investigational treatment cannot be entirely ruled out are to be handled as side effects.

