#### Procedure 2:

Verify if they have had any symptoms through interviews and using checklists. Limit the symptoms to be verified here to the following four symptoms: hypoglycemia, edema, palpitation, and shortness of breath.

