### **12.3.3 Other analyses**

To complement analyses of the primary endpoints, three kinds of analyses (descriptive statistics, hypothesis testing and effect size estimates) are to be performed on the secondary endpoints. However, being exploratory in nature, these analyses are not to be adjusted for multiplicity.

Fisher's direct exact probability estimation is to be used to compare the percentages of occurrence of adverse reactions between the two treatment arms as part of the safety evaluation, and 95% confidence intervals (CI) for the differences detected. Accurate confidence intervals are to be estimated based on the bimodal distribution of the data.

Otherwise, exploratory analyses are to be performed as required. When such analyses are to be performed, their details

are to be described in the Statistical Analysis Plan.

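### Glucose meters are loaned to the intensive arm only, so non-serious hypoglycemia may be ascertained unequally in the between-arm safety comparison

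*Protocol*

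**What the plan says.** **Measurement.** In the intensive arm, "all subjects in the intensive therapy arm are to be loaned a blood glucose meter for self-monitoring of blood glucose (SMBG" (protocol 8.2.1). The same sentence of that section requires doctors to follow the readings: "the physicians in charge are to keep informed of the measured results in these subjects". For the conventional arm, section 8.2.2 sets the glycemic goal and adds only that "the physician in charge is to administer appropriate therapy in accordance with the Guidelines". It mentions no meter. The other home devices are shared: section 8.3 states that "All the subjects in both treatment arms are to be loaned a blood pressure manometer at study entry", and section 8.1.3 does the same for accelerometers.

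**Definition.** Section 11.1 states that "all untoward laboratory findings that occurred after the start of the study are to be handled as adverse reactions". The protocol gives no glucose threshold and no confirmation rule for non-serious hypoglycemia.

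**Collection.** Section 11.2, Procedure 2, has physicians ask about symptoms by interview and checklist: "Limit the symptoms to be verified here to the following four symptoms: hypoglycemia, edema, palpitation, and shortness of breath". Procedure 3 adds laboratory changes and leaves it to the physician to judge which of them matter clinically. The rationale that follows says the procedures are shared by all institutions because the incidence found depends on how it is sought.

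**Seriousness.** One criterion in section 11.4.1 reads "Is serious hypoglycemia accompanied by impaired consciousness".

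**Analysis.** Under section 12.3.3, Fisher's exact method "is to be used to compare the percentages of occurrence of adverse reactions between the two treatment arms", with a 95% confidence interval for the difference. Section 6.1 describes the trial as open-label.

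**The concern.** The arms differ in planned home glucose measurement, and the planned comparison of hypoglycemia makes no allowance for that. A low reading that the subject did not feel, or one that turns a vague complaint into a firm report, can reach the physician in the intensive arm through a device supplied by the trial. The conventional arm has no matching supply. If such readings are recorded as adverse reactions, the two percentages in section 12.3.3 carry a detection difference as well as any treatment difference.

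This bears on a harm the protocol chose to collect actively, because the trial aims at rigorous glycemic control. An excess of non-serious hypoglycemia in the intensive arm would weigh in judging whether the lower HbA1c goal is acceptable. As the plan stands, nobody could say how much of that excess came from the meters. A later analysis could not separate the two either, unless sites record what each report rests on.

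**Working it through.** **Step 1. Planned ascertainment by arm.**

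| Item | Intensive | Conventional | Protocol |
|---|---|---|---|
| Loaned glucose meter | Yes | None stated | 8.2.1, 8.2.2 |
| Loaned manometer | Yes | Yes | 8.3 |
| Loaned accelerometer | Yes | Yes | 8.1.3 |
| Visit interval | At least monthly until March 2010 | None stated | 8.2.1 Note 1, 8.2.2 |
| Glucose at scheduled visits | Yes | Yes | Table 2, 9.3, 9.4 |
| Hypoglycemia checklist | Yes | Yes (not limited to one arm) | 11.2 |

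The asymmetry lies in home glucose data and, in the stated minimum, in visit frequency.

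**Step 2. Route into the comparison.** The definition in 11.1 is broad and has no threshold. Procedure 3 in 11.2 filters laboratory changes by individual judgment. Section 12.3.3 compares the resulting percentages. Nothing in this chain excludes a meter-only report, and nothing requires one.

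**Step 3. Possible size (illustration; every rate is an assumption).** The protocol states no hypoglycemia rate, so there is no figure to reproduce.

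Inputs:
- n = 1,271 per arm (protocol 1.9 and 6.2).
- p = share of subjects with hypoglycemia recorded when no meter plays a part. It is set equal in both arms, so therapy has no effect: 10%, 20% or 40%.
- e = share of the remaining intensive-arm subjects recorded only because of a meter: 0, 2%, 5% or 10%.

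Formula: intensive-arm share p1 = p + (1 − p)e. For example, with p = 10% and e = 5%, p1 = 0.10 + 0.90 × 0.05 = 14.5%, an apparent risk ratio of 14.5/10 = 1.45.

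The chance of two-sided p < 0.05 comes from 1,000 simulated Fisher tests per setting. The normal approximation is in brackets.

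| p | e | p1 | Apparent risk ratio | Chance of p < 0.05 |
|---|---|---|---|---|
| 10% | 0 | 10.0% | 1.00 | 3.9% |
| 10% | 2% | 11.8% | 1.18 | 29.1% (30.7%) |
| 10% | 5% | 14.5% | 1.45 | 92.0% (93.4%) |
| 10% | 10% | 19.0% | 1.90 | 100% (100%) |
| 20% | 0 | 20.0% | 1.00 | 3.8% |
| 20% | 2% | 21.6% | 1.08 | 15.3% (16.7%) |
| 20% | 5% | 24.0% | 1.20 | 66.8% (68.3%) |
| 20% | 10% | 28.0% | 1.40 | 99.5% (99.7%) |
| 40% | 0 | 40.0% | 1.00 | 4.2% |
| 40% | 2% | 41.2% | 1.03 | 9.5% (8.9%) |
| 40% | 5% | 43.0% | 1.07 | 36.0% (33.5%) |
| 40% | 10% | 46.0% | 1.15 | 85.2% (86.4%) |

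The added difference, (1 − p)e, does not depend on n, so a larger trial would not remove it.

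**Step 4. The opposite direction.** Suppose meters also refute the reports of a share r of the subjects in p. Then p1 = p(1 − r) + (1 − p)e, and the two effects cancel when r = (1 − p)e/p. With e = 5%:
- p = 10%: r = 0.90 × 0.05/0.10 = 45%.
- p = 20%: r = 0.80 × 0.05/0.20 = 20%.
- p = 40%: r = 0.60 × 0.05/0.40 = 7.5%.

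Upward bias is the more plausible net result when recorded hypoglycemia is uncommon. It is less secure when it is common.

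**The case against.** The strongest case against the point has five parts.

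- **Hypoglycemia is collected as a symptom.** Procedure 2 and the rationale in 11.2 list it among four symptoms, asked about without limit to one arm. This stands, and the fix builds on it.
- **Home readings are not named as adverse reaction data.** Section 11.1 speaks of laboratory findings, and Procedure 3 passes these through clinical judgment. This also stands. It limits the route without closing it: the judgment has no common threshold, physicians must follow the meter results, and a subject who has seen a low reading can answer yes to hypoglycemia on the checklist.
- **The conventional arm is not blind to glucose.** Glucose is measured at scheduled visits in both arms, and 8.2.2 does not bar meters in usual care. The asymmetry is in what the trial supplies, and its real size is unknown.
- **The meter belongs to the strategy under test.** Readings may prompt correction before an episode develops, which is a genuine effect of that strategy. That is a reason to leave the meters alone. It does not make meter-only reports comparable between arms.
- **Much of this could sit in the analysis plan.** The choice of lead category could. Whether each report's basis is recorded at the site cannot be repaired at the analysis stage, so it belongs in section 11.2.

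**Conclusion.** The point holds in a limited form. With meters loaned to one arm, a definition without a glucose threshold, judgment that is not standardized, and a crude percentage comparison in an open-label trial, non-serious hypoglycemia may be ascertained unequally. The more plausible direction is toward the intensive arm, and the more frequent visits stated for that arm could add to it. This works against the uniform collection that section 11.2 sets out to achieve.

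A reader might infer more: that every low reading counts as an adverse reaction, that the trial's main harm is inflated in one arm, or that the bias has a known direction. The documents do not support this. No rule turns meter readings into adverse reactions, and the protocol does not rank hypoglycemia above the other three checklist symptoms. A meter can also refute a report. Hypoglycemia with impaired consciousness does not need a meter to be noticed and is largely unaffected.

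The chances quoted (roughly 10% to 29% at 2% meter-only recording, 36% to 92% at 5%) rest wholly on assumed rates, an equal underlying share of 10% to 40%, and no refuted reports. They show that small detection differences can matter at this sample size. They do not estimate the bias in this trial.

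**What to change.** **Section 11.2.** Have the case report form state, for each hypoglycemia report, whether it was symptomatic, rested on a meter reading alone, or met the serious criterion in 11.4.1.

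**Section 12.3.3.** Base the between-arm hypoglycemia comparison on two categories: serious hypoglycemia with impaired consciousness, and symptomatic episodes from the checklist collected alike in both arms. Tabulate meter-only reports separately by arm, outside the Fisher comparison.

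**Cost.** One field on an existing form and a few lines of text. Asymptomatic lows would be described and not compared. Meters, treatment and visits do not change.

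**What remains.** The symptomatic category is not fully protected, because a reading can color how a subject describes a vague symptom, and the stated visit intervals differ. The report should say so. The serious category is the firmer of the two.
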